### Procedure

The study’s physical and psychological outcomes will be evaluated at three key intervals: one week before the intervention, at 12 weeks (mid-intervention), and at 24 weeks (post-intervention). Additionally, 20 individuals from each group will be selected randomly for pre-and post-intervention fMRI scanning. The study’s process and timeline are depicted in Figure 1 and Table 1.

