#### Sample size estimation

This preliminary exploratory clinical randomized controlled neuroimaging trial is informed by similar studies and the minimal sample size guidelines for clinical investigations (Yuen et al., 2021). Accounting for a potential 10% dropout rate, we aim to enroll 33 subjects per group, totaling 99 subjects across three groups. A previous neuroimaging study (Szucs and Ioannidis, 2020) indicates that an imaging sample size of more than 15 per group yields reliable and consistent results. Therefore, 20 subjects from each group will be randomly selected for functional magnetic resonance imaging (fMRI) scans.

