### Behavioral analysis

Data analysis will be conducted by an independent statistician using SPSS version 26.0 (SPSS Inc., Chicago, IL, United States). Two-tailed analyzes will be performed, with statistical significance set at *p* < 0.05.

Intention-to-treat analyzes will be applied wherever possible, complemented by subgroup and sensitivity analyzes to identify potential heterogeneity in results. Continuous variables will be expressed as means ± standard deviations, while categorical variables will be presented as numbers and percentages. The normality of continuous variables will be assessed using the Kolmogorov–Smirnov test. For normally distributed data, within-group differences will be evaluated using paired-sample t-tests, and between-group analyzes will employ Analysis of Variance (ANOVA) and the Kruskal–Wallis test. Non-parametric tests will be used for data with skewed distributions.

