### Clinical trial quality control

This study will implement rigorous procedures to mitigate bias and enhance the reliability and reproducibility of the results.

To ensure uniform baseline results among subjects, strict screening and inclusion criteria have been established. Participants must be professionals with completed and verified theoretical and practical training in acupuncture. They should not have engaged in traditional fitness Qigong exercises (such as Baduanjin and Taiji) or mind–body practices (such as yoga and meditation) recently or previously.

For the Baduanjin and aerobic exercise groups, we have defined standardized training protocols, including specific movements, duration, and frequency. Experienced coaches (with over 5 years of practice) will supervise these sessions to guarantee consistency. Training sessions will be video recorded, and random assessments will be conducted to ensure adherence to established standards. The roles of researchers, operators, and statisticians have been distinctly defined, with professional statisticians undergoing specialized training prior to data analysis.

To maintain protocol adherence for all researchers to the study protocol, weekly group meetings will be held for effective communication and continuous learning. After the trial, participants will receive activity credit certificates and reimbursement. Any challenges encountered during the trial will be addressed promptly during these meetings.

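### The between-group tests named in the article carry no baseline adjustment, although every clinical outcome is measured at baseline; naming ANCOVA would recover precision at no cost in data

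*Protocol article*

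**What the plan says.** The Procedure section fixes the visits: physical and psychological "outcomes will be evaluated at three key intervals: one week before the intervention, at 12 weeks (mid-intervention), and at 24 weeks (post-intervention"). Table 1 ticks the baseline, week 12 and week 24 columns for each of the 13 clinical instruments: seven for emotion, attention and cognition, and six for hand motor and sensory function.

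The Behavioral analysis section then fixes the tests. Within each arm, "within-group differences will be evaluated using paired-sample t-tests". Across arms, "between-group analyzes will employ Analysis of Variance (ANOVA"), with the Kruskal–Wallis test named beside it. The section adds that "Two-tailed analyzes will be performed, with statistical significance set at" the 0.05 level, and that skewed data go to non-parametric tests. No ANCOVA, baseline covariate, mixed model or repeated-measures model is named anywhere in the article. The paired t-test is the only named test that must use the baseline value, and it does not compare arms.

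On size, the Sample size estimation section says: "Accounting for a potential 10% dropout rate, we aim to enroll 33 subjects per group, totaling 99 subjects across three groups". It gives no effect size, standard deviation, power or correlation.

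**The concern.** The first objective is a comparison of Baduanjin with aerobic exercise and with a waiting list, so the between-group test answers the trial's main question. In its plain one-way form, ANOVA on a follow-up score leaves all stable differences between people in the error term. The baseline measurement that could remove them is collected but not used in that comparison. With about 30 completers per arm, precision is scarce. Two arms of this size will also often differ somewhat at baseline by chance, and an unadjusted comparison carries part of that difference into the result.

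The section leaves open which variable is analysed. Follow-up score, change from baseline and repeated measures over the visits can all be called ANOVA, and they differ in precision and in how they respond to a baseline imbalance.

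**Working it through.** **The plan's own figure.** 3 × 33 = 99, and 33 × 0.9 = 29.7, or about 30 completers per arm. The arithmetic is consistent. No effect size or power stands behind the 33, so no power formula can reproduce it.

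**Inputs.** From the article: three equal arms, about 30 completers each, two-sided 0.05. Assumed, because the article gives neither: a correlation r of 0.5 to 0.7 between baseline and follow-up (0.3 shown as a low case), and a true pairwise difference of 0.5 SD. Outcome SD is set to 1 at both visits.

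**Variance of an arm comparison, relative to follow-up scores.**
- ANOVA on follow-up scores: 1
- ANOVA on change scores: 2(1 − r). A group-by-time contrast over two visits is the same analysis.
- ANCOVA: 1 − r²

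ANCOVA therefore saves r² of the variance against follow-up scores. Against change scores it saves 1 − (1 − r²)/[2(1 − r)] = (1 − r)/2. The saving in standard error against follow-up scores is 1 − √(1 − r²).

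| r | Change score | ANCOVA | Variance saved vs follow-up | SE saved vs follow-up | Variance saved vs change |
|---|---|---|---|---|---|
| 0.3 | 1.40 | 0.91 | 9% | 5% | 35% |
| 0.5 | 1.00 | 0.75 | 25% | 13% | 25% |
| 0.6 | 0.80 | 0.64 | 36% | 20% | 20% |
| 0.7 | 0.60 | 0.51 | 49% | 29% | 15% |

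**Power.** Pairwise noncentral t, 30 per arm, difference 0.5 SD, error variance pooled over three arms (87 degrees of freedom; 86 for ANCOVA). The noncentrality is 0.5/√(2v/30), where v is the variance factor above. For follow-up scores it is 0.5/0.258 = 1.94.

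| r | Follow-up | Change | ANCOVA |
|---|---|---|---|
| 0.3 | 48.2% | 36.7% | 51.9% |
| 0.5 | 48.2% | 48.2% | 59.9% |
| 0.6 | 48.2% | 57.2% | 66.8% |
| 0.7 | 48.2% | 69.6% | 76.5% |

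In sample-size terms, 30 adjusted completers are worth 30/(1 − r²) unadjusted ones: 40.0 at r = 0.5 and 58.8 at r = 0.7.

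**Chance imbalance.** With 33 per arm, the baseline difference between two arms has standard deviation √(2/33) = 0.246 SD. It exceeds 0.25 SD in 31% of trials for any one pair and outcome. At 30 per arm the figures are √(2/30) = 0.258 SD and 33%. An imbalance of one standard error (0.258 SD) shifts a follow-up comparison by r × 0.258, or 0.13 SD at r = 0.5 and 0.18 SD at r = 0.7. It shifts a change-score comparison by (1 − r) × 0.258 in the opposite direction, or 0.13 SD and 0.08 SD. ANCOVA removes the shift in expectation.

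**The case against.** The best defence is that the article is a condensed text. The Statistical methods section promises a detailed plan for the statisticians, and covariates are commonly settled there. The trial also calls itself preliminary and exploratory and claims no power target. This would answer a complaint about silence, but the section is not silent. It names the method for the between-group comparison, and that method has no baseline term.

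Three stronger readings are tempting, and the article does not support them.

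- *The tests ignore the baseline, at a cost of 25–49%.* This is certain only if follow-up scores are analysed. A change score uses the baseline, and so does a repeated-measures ANOVA over the three visits; the section does not say which is meant. The 25–49% is a variance figure, needs an assumed r of 0.5 to 0.7, and applies to the follow-up reading alone. The three-visit omnibus interaction test has not been quantified here.
- *The false-positive rate is inflated.* Over all randomisations, unadjusted ANOVA is unbiased and keeps its 5% level. With 33 per arm and r = 0.6, the rate is about 17% given a 0.5 SD imbalance between the two arms compared. But 0.5/0.246 = 2.03 standard deviations, so a given pair reaches such an imbalance only about 4% of the time.
- *The quality-control section claims equal arms.* It says: "To ensure uniform baseline results among subjects, strict screening and inclusion criteria have been established". That concerns homogeneity among participants and introduces rules on training and prior practice. It does not claim that randomised arms will match, nor does it offer eligibility as a substitute for adjustment.

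**Conclusion.** The point holds as a recommended improvement to a stated method, not as an error that invalidates the analysis. The direction is firm: under the equal-variance model above, ANCOVA is at least as precise as follow-up scores (apart from one degree of freedom) and more precise than change scores for every r below 1. The size is conditional on r and on which variable enters the ANOVA, and both are unstated. If r turns out near 0.3, the gain over follow-up scores is small, although the gain over change scores is then larger (35% of variance). The power figures rest further on 30 completers per arm, a 0.5 SD difference and an unadjusted two-sided 0.05.

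**What to change.** In the Behavioral analysis section, replace the between-group ANOVA and Kruskal–Wallis with a linear model of the follow-up score on arm and the same outcome's baseline. This can be ANCOVA at a stated visit, or a mixed model over weeks 12 and 24 with baseline as covariate. Report adjusted mean differences between arms with 95% confidence intervals. For skewed outcomes, use ANCOVA on a transformed scale or a rank-based ANCOVA. If the detailed plan already specifies such a model, bring the article's wording into line with it.

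The cost is analysis wording only: the baselines are already scheduled, and no participants need to be added. ANCOVA and mixed models run in the SPSS version already named. The quality-control section needs no change on this account.

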### Neuroimaging data analysis

The fMRI data will be conducted pre-processing in accordance with SPM12^1^ and MATLAB 2013b (MathWorks, Inc., Natick, MA, United States).

Data preprocessing will include discarding the first 5 time-points due to magnetic saturation effects, slice timing, head-motion correction, spatial normalization in Montreal Neurological Institute (MNI) space (resampled at 3 mm × 3 mm × 3 mm voxel size), filtering, and spatial smoothing with an 8-mm FWHM Gaussian kernel.

After preprocessing, the amplitude of low-frequency fluctuation (ALFF), fractional ALFF (fALFF), regional homogeneity (ReHo), functional connectivity (FC), and other brain functional parameters will be analyzed. The 3D-T1 data will be processed using voxel-based morphometry in SPM12 and the CAT12 toolbox in MATLAB (Ashburner and Friston, 2000). DTI data will undergo preprocessing and analysis with the Functional Software Library v4.1.9.^2^ Fractional anisotropy (FA) indices and mean diffusivity (MD) maps will be derived after correcting for head motion and eddy currents in DTI images, followed by tensor model fitting. Correlation analyzes will involve Pearson correlation coefficients between clinical and fMRI data, primarily focusing on functional and structural changes in brain regions associated with emotions, attention, motor skills, and sensory perception.

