### fMRI outcome measurement

MRI data will be acquired using a 3.0-T GE MR750 scanner (GE 3.0 T MR750, Wauwatosa, WI, United States) with an eight-channel phase-array head coil at the University of Electronic Science and Technology of China’s MRI Center.

Scanning parameters include: Structural imaging: Repetition time (TR)/Echo time (TE) = 1900 ms/2.26 ms; slice thickness = 1 mm; 30 slices; matrix size = 128 × 128; field of view (FOV) = 256 × 256 mm. BOLD-fMRI: TR/TE = 2000 ms/30 ms; flip angle = 90°; 30 slices; matrix size = 128 × 128; FOV = 240 × 240 mm; slice thickness = 5 mm; total volume = 240. DTI: TR/TE = 6,800 ms/93 ms; FOV = 240 × 240 mm; matrix size = 128 × 128; slice thickness = 3 mm; two diffusion-weighted sequences with *b* = 1000s/mm^2^ and *b* = 0 across 30 non-collinear directions.

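### As written, fALFF is computed on filtered data and ReHo on data already smoothed at 8 mm, which inflates and compresses ReHo and, if the filter is a band-pass, fALFF too.

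*Protocol article*

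**What the plan says.** The Neuroimaging data analysis section of the protocol article gives one preprocessing sequence for the fMRI data. It begins with "discarding the first 5 time-points due to magnetic saturation effects", goes on through slice timing, motion correction and normalisation ("resampled at 3 mm × 3 mm × 3 mm voxel size"), and finishes with "filtering, and spatial smoothing with an 8-mm FWHM Gaussian kernel". The filter's band and type are not given.

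The next paragraph turns to the functional measures: "After preprocessing, the amplitude of low-frequency fluctuation (ALFF), fractional ALFF (fALFF), regional homogeneity (ReHo), functional connectivity (FC") and others. All of them follow the same sequence. Nothing says that fALFF uses unfiltered data, or that for ReHo the smoothing is applied to the finished map.

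The acquisition settings are in the fMRI outcome measurement section: "BOLD-fMRI: TR/TE = 2000 ms/30 ms" and "total volume = 240".

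**The concern.** Two of the four named functional measures are sensitive to a step that the text places before them.

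- **ReHo** is Kendall's coefficient of concordance (W) between a voxel and its immediate neighbours. Spatial smoothing replaces each voxel by a weighted average of those same neighbours, so part of the concordance then comes from the kernel. At 3 mm, a 27-voxel neighbourhood is a cube of 3 × 3 = 9 mm per side, about the width of the 8 mm kernel.
- **fALFF** is the amplitude in a low-frequency band divided by the amplitude over the whole measurable spectrum. A temporal filter deletes part of that denominator. If the filter passes only the numerator band, numerator and denominator become the same quantity.

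Both measures feed the group comparisons behind the brain-function objective and the planned Pearson correlations with clinical data. The correlations are exposed because they depend on how far the measure varies between subjects.

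**Working it through.** The article states no figure on this point, so there is none to reproduce. The check applies the stated settings to simulated data.

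**Inputs from the article**
- Repetition time 2 s, so the highest measurable frequency is 1/(2 × 2) = 0.25 Hz.
- Volumes retained: 240 − 5 = 235. Frequency spacing is 1/(235 × 2) = 0.00213 Hz, giving 117 non-zero frequencies.
- Voxel size 3 mm; smoothing kernel 8 mm FWHM.

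**Assumptions (not in the article)**
- fALFF numerator band 0.01–0.08 Hz.
- Filter: 0.01–0.08 Hz band-pass, 0.01–0.10 Hz band-pass, or 0.01 Hz high-pass only.
- ReHo neighbourhood of 27 voxels.

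**ReHo**

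Kernel SD: σ = 8/2.355 = 3.40 mm. After smoothing, two independent-noise voxels at distance d have correlation exp(−d²/(4σ²)):
- face neighbour, d² = 9: 0.82
- edge neighbour, d² = 18: 0.68
- corner neighbour, d² = 27: 0.56

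Kendall's W for K = 27 voxels and T = 235 volumes is W = 12 Σ(Rᵢ − R̄)² / [K²(T³ − T)], where Rᵢ is the sum of ranks at time i. For independent series its expected value is 1/27 = 0.037. Adding a common signal of rising weight to unit-variance noise gives:

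| Shared-signal weight | W, unsmoothed | W, after 8 mm smoothing |
|---|---|---|
| 0 (noise only) | 0.037 | 0.50 |
| 0.3 | 0.11 | 0.92 |
| 0.6 | 0.28 | 0.98 |
| 1.0 | 0.49 | 0.99 |

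Repeat runs put the smoothed noise value at 0.48–0.50. Band-passing at 0.01–0.08 Hz before smoothing gives practically the same figures, so this result does not hinge on the filter. Smoothed noise scores about what strong shared signal scores unsmoothed. The spread across the three signal weights shrinks from 0.49 − 0.11 = 0.38 to 0.99 − 0.92 = 0.07.

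**fALFF**

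fALFF = Σ amplitude in 0.01–0.08 Hz / Σ amplitude over all non-zero frequencies. For white noise every frequency has the same expected amplitude, so counting frequencies gives the answer:
- unfiltered: 33/117 = 0.28
- 0.01–0.08 Hz band-pass: 33/33 = 1.00
- 0.01–0.10 Hz band-pass: 33/43 = 0.77
- 0.01 Hz high-pass: 33/113 = 0.29

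Simulated first-order autoregressive series with ideal filters extend this to signals with more low-frequency content:

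| Autoregressive coefficient | Unfiltered | 0.01–0.08 Hz | 0.01–0.10 Hz | High-pass 0.01 Hz |
|---|---|---|---|---|
| 0 | 0.28 | 1.00 | 0.77 | 0.29 |
| 0.3 | 0.36 | 1.00 | 0.80 | 0.38 |
| 0.6 | 0.44 | 1.00 | 0.84 | 0.48 |
| 0.9 | 0.48 | 1.00 | 0.89 | 0.59 |

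In the 0.01–0.08 Hz column the SD is zero: every series gives the same value. A gradual filter over that band (second-order Butterworth, run forwards and backwards) gives 0.78–0.86, which is compressed but still in the right order.

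**The case against.** Four points can be made for the plan.

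1. **The fALFF effect depends on an unstated filter.** This stands. The complete loss needs an ideal filter whose band equals the numerator band. A gradual filter keeps the ranking, and a high-pass alone changes fALFF only slightly to moderately.

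2. **The ReHo shift is common to all arms and both scans.** This also stands. One kernel applied to everyone does not produce a difference between randomised groups. W is compressed towards its ceiling, but so is its SD. In a simple simulation (one shared signal, no between-subject variance, 40 runs per setting, assumed 0.01–0.08 Hz band), the standardised difference between neighbouring signal weights, unsmoothed against smoothed, was 2.35 against 2.33 and 1.99 against 1.77 for spatially broad signal. For a small local patch it was 1.79 against 1.58 and 1.60 against 1.18. The loss therefore runs from about 1% to (1.60 − 1.18)/1.60 = 26%, larger for local signal. A reader might infer that smoothed ReHo is pure artefact; these figures do not support that.

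3. **A reader might infer that H2 can no longer be tested.** The article does not support that either. H2 concerns both structure and function, and ALFF, functional connectivity, voxel-based morphometry, fractional anisotropy and mean diffusivity are also planned and not touched by this argument.

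4. **An article condenses, and the Statistical methods section promises a detailed plan.** This excuses the missing filter band. It does not fully answer the point, because the article does state an order, and that order, followed literally, gives the results above. If the pipeline in fact branches by measure, the published description still needs correcting.

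**Conclusion.** The point holds in limited form. The stated order is unsuitable for ReHo, and for fALFF if the filter is a band-pass.

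- **ReHo:** noise moves from about 0.04 to about 0.5 and real shared signal to 0.92–0.99. The measure is inflated and compressed and can lose sensitivity and local specificity; it is not emptied of information. This rests on the stated voxel size and kernel plus the 27-voxel neighbourhood.
- **fALFF:** the outcome ranges from total loss of information (ideal filter matching the numerator band), through strong compression, to a small or moderate change (high-pass only). The article does not say which case applies.

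The consequence is confined to two mechanistic measures, and their clinical correlations, in 20 scanned participants per group of a trial that describes itself as exploratory. The behavioural primary outcomes are not involved. It is worth correcting before the images are analysed, but it does not threaten the trial.

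**What to change.** In the Neuroimaging data analysis section, or in the analysis plan with the article's description corrected to match:

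- state the filter type and band;
- say that fALFF is computed on data that have not been band-pass filtered;
- say that ReHo is computed on filtered but unsmoothed data, and that the resulting ReHo maps are then smoothed.

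Nothing shown here requires a change for ALFF or functional connectivity. The cost is a few sentences and a small change to the processing script, with no new data, scans or burden on participants.

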## Discussion

This study represents the first exploration into the patterns and mechanisms associated with Qigong practice among acupuncturists. Its outcomes will contribute initial insights into the effects of Qigong on emotional and attention control while revealing neuroimaging mechanisms unique to acupuncturists. Additionally, these findings will provide empirical support for integrating Qigong into strategies aimed at enhancing acupuncturists’ skills.

### Clinical trial quality control

This study will implement rigorous procedures to mitigate bias and enhance the reliability and reproducibility of the results.

To ensure uniform baseline results among subjects, strict screening and inclusion criteria have been established. Participants must be professionals with completed and verified theoretical and practical training in acupuncture. They should not have engaged in traditional fitness Qigong exercises (such as Baduanjin and Taiji) or mind–body practices (such as yoga and meditation) recently or previously.

For the Baduanjin and aerobic exercise groups, we have defined standardized training protocols, including specific movements, duration, and frequency. Experienced coaches (with over 5 years of practice) will supervise these sessions to guarantee consistency. Training sessions will be video recorded, and random assessments will be conducted to ensure adherence to established standards. The roles of researchers, operators, and statisticians have been distinctly defined, with professional statisticians undergoing specialized training prior to data analysis.

To maintain protocol adherence for all researchers to the study protocol, weekly group meetings will be held for effective communication and continuous learning. After the trial, participants will receive activity credit certificates and reimbursement. Any challenges encountered during the trial will be addressed promptly during these meetings.

### Quality control of imaging tests

In this study, participants aged between 18 and 25 years and who are right-handed will be selected to minimize confounding effects on brain function and structure related to age and handedness. In addition, all neuroimaging scans will be conducted using the same scanner operated by an expert professional.

Before scanning, subjects will receive comprehensive information about the process and environment, along with an emotional assessment. They will be advised to avoid excessive exercise, late nights, and the consumption of alcohol, tobacco, tea, and coffee for 3 days before the scan. During the scan, subjects will wear sponge earplugs and have foam padding around their heads to limit movement. They will be instructed to keep their eyes closed but remain awake. The scanning room will be maintained at 18°C–22°C with humidity above 60% and noise levels below 150 dB.P After the scan, the data will undergo thorough review by professionals, and any data affected by artifacts, signal loss, distortion, or noise interference due to head movement will be excluded from the analysis.

